### Data analysis

#### Rate of change in heart rate

The rate of change in heart rate and pupil diameter before and after both the taVNS and sham stimulation will be calculated. A one-sample test will be performed for the difference between the two stimuli (during taVNS vs. during sham stimulation). The effects of stimulus order will also be evaluated by group.

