**Methods:**

This protocol employs a single-blind, randomized cross-over design involving 10 healthy male participants. Simultaneous assessment of both the afferent and efferent aspects of the vagus nerve will be performed by integrating physiological measures, magnetic resonance imaging, and a questionnaire survey. Electrocardiogram will be measured to assess changes in heart rate, as a primary outcome, and heart rate variability. Active taVNS and sham stimulation will be compared, which ensures precision and blinding. Electrical stimulation will be applied to the left *concha cymba* and the left *lobule* for the active and sham conditions, respectively. The specific parameters of taVNS involve a pulse width of 250 µs, a frequency of 25 Hz, and a current adjusted to the perception threshold (0.1 mA ≤ 5 mA), delivered in cycles of 32 s on and 28 s off.

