### Procedures

#### Experimental design

A single-blind randomized cross-over design will be used. Random assignment will be performed using a computer-generated randomization system by an institutional Academic Research Organization section to determine whether the participants would be assigned to the target or sham session first.

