#### Cross-over evaluations

The same set of evaluations will be conducted at intervals of at least 1 week (details shown in the *Interval Considerations* section below). Stimulation methods will be crossed to account for any variations.

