#### Interval considerations

An interval of at least 1 week will be maintained to eliminate the potential carryover effect of taVNS (15-min stimulation). Previous studies employing crossover designs have utilized various stimulus intervals, including 50-min stimulation, 48-h interval [10]; 4-min stimulation, 1-week interval [11]; and 30-min stimulation, 1-week interval [12]. Based on the fact that prior studies set a maximum of 1 week to eliminate the carryover effect, we also set a 1-week interval in the present study, thereby aligning with previous practices.

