### Physiological measures

#### ECG

ECG will be measured using a two-lead ECG acquisition device (BrainAmp; Brain Products GmbH, Gilching, Germany) in order to assess changes in heart rate, as a primary outcome, and HRV. ECG data will be recorded using two disposable sticker-type electrodes, one on the left arm and one on the right arm, and another electrode on the right leg.

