#### Brain imaging data

A general linear model will be used to identify brain regions and circuits that show significant correlations with pre- and post-stimulus changes in each index during taVNS and sham stimulation. T1-weighted images will be used to identify the location of the nucleus tractus solitarius, locus coeruleus, anterior insular cortex, anterior cingulate cortex, and amygdala, serving as seeds to assess functional brain connectivity at rest. Resting-state functional brain connectivity will also be evaluated, using the anterior insular cortex as a seed. Statistical adjustments for age and other factors will be made when evaluating indices that differ between changes during taVNS stimulation and changes during sham stimulation. Additional analyses will be performed when deemed necessary or meaningful.

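### The primary heart-rate test has no period term, so a first-versus-second-visit difference in response would cost power at 5:5 and bias the estimate if the sequences are unequal

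*Protocol article*

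**What the plan says.** The design is a two-session cross-over: "This protocol employs a single-blind, randomized cross-over design involving 10 healthy male participants" (Protocol article, abstract, Methods). Under Experimental design, a computer-generated system is used "to determine whether the participants would be assigned to the target or sham session first". The article does not say whether the sequence list is balanced or blocked.

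Heart rate is the primary outcome; the ECG section says the recording is made "in order to assess changes in heart rate, as a primary outcome, and HRV". Each visit has its own pre-stimulation recording, because under Cross-over evaluations "The same set of evaluations will be conducted at intervals of at least 1 week".

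Under Data analysis, Rate of change in heart rate, a change is computed for each stimulus and then tested: "A one-sample test will be performed for the difference between the two stimuli (during taVNS vs. during sham stimulation". The next sentence adds "The effects of stimulus order will also be evaluated by group". Carryover is handled by washout: "An interval of at least 1 week will be maintained to eliminate the potential carryover effect of taVNS (15-min stimulation".

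**The concern.** Each participant contributes one taVNS-minus-sham difference. In those who have taVNS first, a first-visit effect on the response adds to this difference; in those who have sham first, it subtracts. A one-sample test sees only the pooled spread and the pooled mean. With equal sequences, the period effect cancels in the mean but remains in the error variance. With unequal sequences, part of it also remains in the mean.

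The randomised order already supplies what is needed to remove this effect, but the stated primary test does not use it. With 10 participants there is little power to spare. The separate look at order comes without a stated link to the primary estimate, so it cannot protect that estimate.

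**Working it through.** **Inputs from the article.** N = 10, two sequences, two periods, and a one-sample test on the within-person difference. No effect size, SD, significance level or power is given, so N = 10 cannot be reproduced from the article.

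**Assumptions.** Two-sided 5% level; normal differences with SD 1 within sequence; true effect τ = 0.8 SD; period effect π from 0 to 1.0 SD. Here π is the first-minus-second-visit difference in the heart-rate change.

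**Model.** The mean of D = taVNS change − sham change is τ + π with taVNS first (n1 participants) and τ − π with sham first (n2 participants).

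**Two estimates.**
- Planned: the mean of all 10 D. Its expectation is τ + π(n1 − n2)/10. The expected sample variance is 1 + (10/9)π²[1 − ((n1 − n2)/10)²]. It has 9 df and critical t 2.26.
- Period-adjusted: half the sum of the two sequence means. Its expectation is τ for any split. SE = s_pooled × √(1/n1 + 1/n2)/2, with 8 df and critical t 2.31.

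**Balanced 5:5.** There is no bias. At π = 0.5 the variance of D in the planned test is 1 + (10/9)(0.25) = 1.28; at π = 1.0 it is 2.11. Power for the period-adjusted test is exact: noncentrality 0.8 × √10 = 2.53 on 8 df gives 60.3%, whatever π is. For the planned test, power at π = 0 is exact and the rest is simulated, as is type I error.

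| π (SD) | Planned: power | Period-adjusted: power | Planned: type I error |
|---|---|---|---|
| 0 | 62% | 60% | 5.0% |
| 0.25 | 59% | 60% | 4.4% |
| 0.5 | 52% | 60% | 3.0% |
| 0.75 | 41% | 60% | 1.6% |
| 1.0 | 28% | 60% | 0.7% |

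At π = 0 the unrounded figures are 61.6% and 60.3%, a cost of 1.3 points.

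**Unequal sequences, π = 0.5.**

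| Split | Bias = π(n1 − n2)/10 | Planned: type I error | Period-adjusted: type I error |
|---|---|---|---|
| 6:4 | 0.5 × 0.2 = 0.10 SD | about 4% | about 5% |
| 7:3 | 0.5 × 0.4 = 0.20 SD | about 6% | about 5% |
| 8:2 | 0.5 × 0.6 = 0.30 SD | about 11% | about 5% |

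**How likely are these splits?** Under simple 1:1 randomisation (an assumption), 5:5 has probability 252/1024 = 24.6%, 6:4 either way 41.0%, 7:3 either way 23.4%, and 8:2 or worse 112/1024 = 10.9%. Averaged over such draws, the planned test's type I error is 5.0% at π = 0.5 and 5.2% at π = 1.0.

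**Can the separate order evaluation rescue the test?** Comparing D between 5 and 5 participants (8 df) has 80% power at a difference of 2.02 SD. The sequence means differ by 2π, so this corresponds to π of about 1.0 SD. At π = 0.5 the noncentrality is 1.0 × √2.5 = 1.58 and power is about 29%. A null result would therefore say little.

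**The case against.** A reader might infer that the plan ignores order altogether. It does not. Comparing the two sequence groups on the taVNS-minus-sham difference is the period comparison in this design, and the article announces an evaluation of order by group. What stands is narrower: that evaluation is not stated to feed into the primary estimate. Model terms are often left to an analysis plan that is not shown here, but the article does name the primary test.

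A reader might also infer that any first-visit novelty spoils the result. Each visit has its own baseline, so a constant shift in heart rate cancels in an absolute change and nearly cancels in a proportional one. Only a period effect on the within-visit response survives. Settling down during an unfamiliar first session could produce one, but the article offers no evidence of it, and 0.5 SD or more is large beside a treatment effect of 0.8 SD. The section does speak of change before and after stimulation and then compares values during stimulation. If the latter were compared directly, a constant visit shift would enter as well, so that wording needs reconciling.

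A third tempting reading is that the error rate is inflated to 10–20%. That needs an 8:2 split and a period effect of 0.5 to 1.0 SD. At 5:5 and 6:4 the test is conservative. The article does not say that simple randomisation is used, and a condensed article may omit blocking.

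Finally, one might fault the change score and ask for the session baseline as a covariate. The documents do not support this. They give no pre/during correlation, and with 10 participants baseline regression can lose about 4 points of power when that correlation is high.

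**Conclusion.** The point holds in a conditional form. The stated primary test omits the period, and the separate order evaluation is too weak at this size to justify leaving it out. If the response does not differ between visits, nothing is lost. If it does, a 5:5 trial remains unbiased but gives up about 1 point of power at 0.25 SD, 9 points at 0.5 SD and 32 points at 1.0 SD, for a true effect of 0.8 SD. Bias arises only with unequal sequences and is a statement about the realised split; over repeated simple randomisation the test is close to its nominal level. The period effects, the treatment effect and the normal model are assumptions, because the article supplies no figures. This calls for a change in the analysis wording; it does not show that the planned test is invalid.

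**What to change.** State the primary estimate as half the sum of the two sequence-mean taVNS-minus-sham differences, with the pooled within-sequence variance on 8 df. A model with condition, period and participant is equivalent. Confirm that the sequence list is balanced 5:5. Report the order effect descriptively, and do not use it to choose between an adjusted and an unadjusted analysis. If an analysis plan already contains a period term, align the article's wording with it.

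The cost is one degree of freedom, or about 1 point of power at 5:5 when there is no period effect. Balance matters to this cost. For a true effect of 0.8 SD, the noncentrality of the adjusted test is 1.6/√(1/n1 + 1/n2). It falls from 2.53 at 5:5 to 2.48 at 6:4, 2.32 at 7:3 and 2.02 at 8:2, and power falls from 60% to about 59%, 53% and 43%. No change to visits, measurements or sample size is needed.

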#### HRV

As indices of HRV in the time domain, we will use the mean value of the R-R interval (i.e., the interval between R-wave peaks in the ECG), the standard deviation of the R-R interval, the root mean square of the difference between adjacent R-R intervals, and the number of heartbeats with an R-R interval of 50 ms or longer. The power spectral density of the R-R interval data will be analyzed, and the power in the low-frequency range (LF), power in the high-frequency range (HF), and the LF/HF ratio will be used as indices in the frequency domain. For HRV analysis, analysis of variance will be performed for two factors: (1) pre- and post-stimulus and (2) during taVNS stimulation.

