## Background

The autonomic nervous system (ANS) plays an indispensable role in various physiological functions, including cardiovascular activity, visceral perception, and emotional states [1]. Maintaining homeostasis relies on the delicate balance between the sympathetic and parasympathetic branches of the ANS [2]. Transcutaneous auricular vagus nerve stimulation (taVNS) has emerged as a cutting-edge tool to elucidate the mechanisms of autonomic regulation [3]. As a linchpin of the parasympathetic system, the vagus nerve’s extensive connections with the central nervous system positions it at the core of autonomic control [4]. Recent advancements underscore the potential of taVNS to modulate autonomic activity and influence functions such as heart rate and heart rate variability (HRV) [5, 6]. To gain a more comprehensive understanding, it is imperative to integrate these validated insights by examining indices of the afferent (e.g., brain magnetic resonance imaging [MRI]) and efferent (e.g., heart rate, pupil diameter) branches.

Offering a non-invasive approach with therapeutic potential, taVNS holds promise for addressing autonomic dysregulation [3]. The present study employs a comprehensive approach that integrates physiological, neural, and perceptual assessments to unravel the intricate influence of taVNS on autonomic functions, bridging the gap between theoretical understanding and clinical application. The study aims to investigate the proof of mechanism (POM) behind taVNS, focusing specifically on heart rate as a primary outcome and HRV and brain MRI as key indicators of vagal influence on the efferent and afferent tracts, respectively. Building on prior findings, this study investigates the immediate effects of taVNS intervention on autonomic functions through the use of a stimulus variable known for heart rate modulation.

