In the present study, we aim to enhance the specificity of our investigation by adopting a stimulus variable known to induce a more potent effect on heart rate reduction (25 Hz). Focusing on the short-term effects as the primary evaluation criterion, we anticipate detecting a reduction in heart rate in 10 cases by focusing on male subjects to exclude the effect of differences by sex. Because empirical evidence has demonstrated the impact of the menstrual cycle on the vagal nerve system [8, 9], this strategic approach of restricting the participants to men allows for a more nuanced understanding of the immediate impact of taVNS on heart rate dynamics by controlling the potentials that confounds such effects. Therefore, in this study, we will conduct a sham-controlled, single-blind randomized controlled trial targeting a healthy population, with the aim of pinpointing the POM for taVNS. The adoption of a single-blind study design ensures that participants remain unaware of whether they are receiving actual taVNS stimulation or a placebo intervention. This rigorous methodology was chosen to provide a thorough insight into the mechanisms underlying the effects of taVNS in a healthy population.

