## Methods

### Participants

Ten healthy male participants will be recruited via internal advertisement at the institute where the research is to take place. The inclusion criteria include healthy males aged 20–39 years. Exclusion criteria are smokers, individuals with regular medication intake, a history of glaucoma or cerebrospinal fluid shunt surgery, and auricular hematoma (to facilitate the placement of taVNS electrodes). Participants will also be screened for MRI exclusion criteria, including nonremovable metal parts in/on the body, tattoos, known neurological diseases, and claustrophobia. Eligibility and exclusion criteria will be assessed through a physician interview. Participants deemed eligible have already been approached for written consent.

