#### Stimulation phase

Physiological parameters (ECG; pupil diameter. 15 min; heartbeat perception task. 5 min) will be measured under stimulation. MRI (rest, 15 min) will also be performed during stimulation.

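### One HRV index puts the 50 ms threshold on the R-R interval itself, so it counts every heartbeat and carries no variability information

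*Protocol article*

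**What the plan says.** The HRV section of the protocol article names four time-domain indices and three frequency-domain indices (low-frequency power, high-frequency power and their ratio), seven in all. The time-domain list opens with "As indices of HRV in the time domain, we will use the mean value of the R-R interval" and explains the R-R interval as "the interval between R-wave peaks in the ECG", that is, one full cardiac cycle. The standard deviation of the R-R interval comes second. The third index is "the root mean square of the difference between adjacent R-R intervals". The fourth is "the number of heartbeats with an R-R interval of 50 ms or longer".

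No other section redefines the fourth index. The Background gives HRV a collective role, describing "HRV and brain MRI as key indicators of vagal influence on the efferent and afferent tracts, respectively". It also states the expected direction for heart rate: "we anticipate detecting a reduction in heart rate in 10 cases". The Brain imaging data section plans a general linear model that relates brain regions and circuits to pre- to post-stimulus changes in every index.

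**The concern.** The fourth index is presented as a measure of heart rate variability, but its threshold sits on the length of the interval and not on the change from one interval to the next. On the article's own definition of the R-R interval, the rule excludes nothing. A programmer who followed it would produce a beat count labelled as HRV.

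Three things follow. The index would duplicate information already held by the primary outcome and by the first index in the list. A change in it would reflect heart rate alone, yet would be reported under HRV. And because the imaging models draw on changes in all the indices, a mislabelled heart-rate count could enter them as though it were a vagal variability measure.

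**Working it through.** **Inputs from the article.** The threshold is 50 ms, applied to the R-R interval (HRV section). The R-R interval is the time between R-wave peaks (same sentence). Population: "The inclusion criteria include healthy males aged 20–39 years" (Participants). Recording under stimulation: "Physiological parameters (ECG; pupil diameter. 15 min; heartbeat perception task. 5 min) will be measured under stimulation" (Stimulation phase). The punctuation leaves it slightly open whether the 15 min covers the ECG as well as the pupil recording; I take it that it does, with equal windows at each phase.

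**Step 1. Which beats meet the rule?** Heart rate = 60,000 / R-R (ms). At 50 ms this is 60,000 / 50 = 1200 beats/min. Conversely:

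| Heart rate (beats/min) | R-R (ms) | Meets the rule? |
|---|---|---|
| 40 | 1500 | yes |
| 70 | 857 | yes |
| 100 | 600 | yes |
| 220 | 273 | yes |

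Every physiological beat qualifies. This step needs no assumption.

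**Step 2. What does the index then measure?** In a window of fixed length, count = heart rate × minutes. For 15 min this gives 15 × 70 = 1050 at 70 beats/min and 15 × 65 = 975 at 65 beats/min. Equivalently, count ≈ 900,000 ms / mean R-R. The index is a rescaling of heart rate and of the reciprocal of mean R-R. Divided by the number of beats, it is 100% in every record.

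**Step 3. How would a difference-based index behave? (illustrative only)** The mean R-R and variability values below are assumptions; none is in the article.

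*Illustration A.* Successive differences are taken as normal with mean zero and standard deviation equal to the root mean square difference (RMSSD), so P(|difference| > 50 ms) = 2[1 − Φ(50 / RMSSD)].
- Mean R-R 900 ms, RMSSD 40 ms: 900,000 / 900 = 1000 beats; 2[1 − Φ(1.25)] = 21%, about 211 pairs.
- Mean R-R 950 ms, RMSSD 50 ms: 900,000 / 950 ≈ 947 beats; 2[1 − Φ(1)] = 32%, about 300 pairs.

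The index as written goes from 1000 to 947, a fall of 5%. The difference-based count goes from about 211 to about 300, a rise of about 42%.

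*Illustration B.* Simulated 15-min series, 100 replicates each, with a respiratory oscillation plus random noise:

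| Assumed mean R-R / oscillation amplitude / noise SD (ms) | Count as written | Share of beats | Adjacent differences > 50 ms |
|---|---|---|---|
| 857 / 30 / 15 | 1051 | 100% | 148 (14%) |
| 896 / 45 / 18 | 1006 | 100% | 352 (35%) |
| 923 / 55 / 20 | 977 | 100% | 466 (48%) |

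The rise in the difference-based count runs from 42% in A to roughly threefold in B (466 / 148 ≈ 3.1), purely because the assumed variability differs. Only the direction is informative, and only for a heart that slows while its beat-to-beat variability increases.

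**The case against.** The best case for the plan is that a few words have dropped out. The index just before it is written on differences between adjacent intervals, and 50 ms is not a usable cutoff for a whole interval. An experienced analyst, or standard HRV software, would probably compute the difference-based count anyway. The primary outcome and the other six HRV indices are not affected, and one of those six, the root mean square of successive differences, already captures beat-to-beat variability. All of this stands, and it limits the severity. It does not make the sentence right: the article gives an explicit operational rule, the rule is wrong, and nothing elsewhere corrects it. Nor is this a detail left to a fuller document, since the definition is present and not omitted.

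A reader might infer something stronger: that the index runs opposite to vagal tone and would reverse the study's efferent conclusion. The article does not support that. The opposite movement needs a raw count, windows of equal length and a heart rate that actually falls over the window; the Background describes earlier heart-rate and HRV effects as lasting only 30–60 s. As a proportion, the index does not move at all. A reversed conclusion would further require that nobody notices every beat qualifying, and that this one index is read ahead of the six others. The Background's description of HRV as a key indicator concerns HRV as a whole and is not itself in error.

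**Conclusion.** The definition is wrong as written. The index equals the total beat count, duplicates heart rate and mean R-R, and holds no variability information. That conclusion rests only on 60,000 / 50 = 1200 beats/min and the article's own definition of the R-R interval.

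Its reach is one of seven secondary HRV indices, together with any imaging model that uses that index. The primary outcome is untouched. Minor to moderate severity is the fair rating: the plan cannot be followed literally on this index, but no primary test depends on it. The illustrative magnitudes depend on assumed inputs and should not be quoted as an expected effect. The article does not use the name NN50; that the standard index of that name was meant is an inference from the 50 ms threshold and its place in the list. The finding does not depend on that inference.

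**What to change.** Replace the fourth time-domain index with: the number of pairs of adjacent R-R intervals that differ by more than 50 ms. This moves the threshold to the difference and also changes the inequality from at-least to strictly greater; the sponsor should confirm the strict form, though the choice matters little in practice.

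Preferably, also express the result as a percentage of all adjacent pairs, because the raw count still depends on the number of beats and hence on heart rate. This is optional and not needed to cure the error.

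Check that the analysis code and the index list feeding the imaging models use the corrected definition. The cost is one line of text and at most one line of code; no change to data collection, sample size or the primary analysis is needed.

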#### Percentage change in pupil diameter

The rate of change in pupil diameter during taVNS stimulation and during sham stimulation will be calculated. A one-sample test will be performed to analyze the difference between the two stimuli (during taVNS stimulation vs. during sham stimulation). The effects of stimulus order will be evaluated by group.

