#### Behavioral and psychological measures

The relation between the rate of change in internal perception, physical symptoms, and psychiatric symptom scale as well as the rate of change during taVNS and sham stimulation will be evaluated using analysis of variance and statistical modeling.

To this end, the MAIA, STAI, and SSS-8 will be analyzed by performing a *t*-test for each total score and sub-score, by comparing taVNS and sham sessions. Additional analyses will also be performed when deemed necessary or significant.

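### The HRV analysis of variance names no sham condition, and its second factor has no comparator level, so as written it cannot separate a taVNS effect from change over the session

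*Protocol article*

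**What the plan says.** Under Data analysis, the HRV section lists time-domain and frequency-domain indices and then gives the test: "analysis of variance will be performed for two factors: (1) pre- and post-stimulus and (2) during taVNS stimulation". Sham does not appear in that section, and no interaction is named.

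The rest of the protocol article is built around sham:

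- Experimental design: "A single-blind randomized cross-over design will be used". Each man has one target and one sham session, and Cross-over evaluations has the same measurements repeated in the second.
- Abstract, Methods: "Active taVNS and sham stimulation will be compared". This comes after the ECG has been introduced as the source of both heart rate and HRV.
- Rate of change in heart rate: "A one-sample test will be performed for the difference between the two stimuli (during taVNS vs. during sham stimulation").
- Percentage change in pupil diameter: "A one-sample test will be performed to analyze the difference between the two stimuli (during taVNS stimulation vs. during sham stimulation").
- Brain imaging data: changes under taVNS and under sham are both brought into the analysis.
- Behavioral and psychological measures: questionnaire scores are tested "by comparing taVNS and sham sessions".

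The Background makes heart rate the primary outcome and HRV a key indicator on the efferent side.

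**The concern.** A factor in an analysis of variance needs at least two levels. Being under taVNS stimulation is one phase of one session. It cannot be crossed with pre/post, because a pre- or post-stimulation recording is by definition not made during stimulation. An analyst who follows the sentence has two choices. One is a model that cannot be fitted as a two-factor design. The other is a comparison of phases (pre, during, post) within the taVNS session alone.

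The second choice gives up the control that the cross-over was set up to provide. HRV may change over a session for reasons such as rest, fatigue or habituation. Without the sham session in the model, that change and a taVNS effect fall into the same term. A significant time effect would then not be evidence of vagal modulation, although HRV is one of the indices on which the article rests its proof of mechanism.

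**Working it through.** **1. The sections side by side.**

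| Outcome (section) | Sham named in the analysis? |
|---|---|
| Heart rate, primary (Rate of change in heart rate) | Yes, taVNS versus sham |
| Pupil diameter (Percentage change in pupil diameter) | Yes, taVNS versus sham |
| Brain imaging (Brain imaging data) | Yes |
| Questionnaires (Behavioral and psychological measures) | Yes, taVNS and sham sessions |
| HRV (HRV) | No |

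HRV is the only exception, and no other section supplies a sham factor for its model.

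**2. What each contrast estimates.** Let δ be the average change over the session unrelated to stimulation, and τ the taVNS effect.

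- Change in the taVNS session alone: δ + τ.
- Change in the sham session: δ, if drift is the same in both sessions and sham has no effect of its own.
- Difference of the two changes, which is the condition-by-time interaction: (δ + τ) − δ = τ.

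Only the last isolates τ.

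**3. Size of the problem, as an illustration.** The article states no alpha, effect size, HRV variability or drift, so it has no figure of its own to reproduce. Inputs:

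- n = 10, from Participants: "Ten healthy male participants will be recruited via internal advertisement".
- Assumed: two-sided alpha 0.05, normally distributed changes, independent changes in the two sessions, no taVNS effect (τ = 0).
- Assumed: drift d = δ / SD of the within-person post-minus-pre change, at 0.3, 0.5 and 1.0.

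The pre/post test within the taVNS session has statistic t = mean change / (SD/√n). It follows a noncentral t distribution with n − 1 = 9 degrees of freedom and noncentrality d√n. The critical value is 2.262, and the rejection probability is P(|t| > 2.262).

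| d | d√10 | Rejection, taVNS session only |
|---|---|---|
| 0 | 0 | 5.0% |
| 0.3 | 0.949 | 13.6% |
| 0.5 | 1.581 | 29.3% |
| 1.0 | 3.162 | 80.3% |

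**4. A test closer to an analysis of variance.** A simulated three-phase repeated-measures analysis of variance (pre, during, post) within the taVNS session, with linear drift that totals d from pre to post, rejects in 5%, 23% and 74% of trials at d = 0, 0.5 and 1.0. The pattern is the same and slightly milder.

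**5. With sham in the model.** The simulated test of the taVNS change minus the sham change rejects in 4.9% to 5.0% of trials over d from 0 to 1.0.

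**The case against.** The strongest reply is that this is a slip of wording. The literal model is not coherent, so it is unlikely to be a deliberate sham-free plan. The heart rate and pupil sections give the full phrase, with taVNS set against sham. Restoring the missing half in the HRV section gives time by stimulus, which is close to what is asked for here. The abstract also promises an active-versus-sham comparison. This may well be right, and the documents do not show that the sponsor means to leave sham out. Even so, the written sentence is wrong and permits an uncontrolled claim. The repaired sentence would also have to name the interaction, because a main effect of time does not isolate taVNS.

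The second reply is that the rejection rates rest on drift sizes that the article does not give and on a paired test that it does not state. That stands, and the rates are only an illustration. That the sham contrast stays near 5% depends on equal drift in both sessions, which is also an assumption.

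Three stronger readings are tempting but not supported:

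- **That the efferent side of the study loses its control.** Heart rate and pupil diameter are efferent indices too, and both have an explicit sham contrast.
- **That skewed HRV indices will be analysed untransformed.** The HRV section is silent on transformation, and an article may leave that to the full plan.
- **That the baseline blocks (40 + 15 + 5 = 60 min) measure the room for drift.** What matters is the interval between the pre-stimulation ECG and the later ones. The total includes that first ECG block, and Baseline assessment (pre) does not clearly fix the order.

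**Conclusion.** The point holds in a limited form. The HRV section misstates its model: the second factor has no comparator, sham is missing, and this contradicts the design and every other outcome analysis in the article. Followed literally, the analysis either cannot be fitted or tests change over time without a control. In the second case, false-positive findings could rise from 5% to roughly 14%, 29% or 80% under assumed drifts of 0.3, 0.5 or 1.0 SD. The direction of the error does not depend on those assumptions, but its size does.

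The consequence is confined to one outcome family that is non-primary but is called key. The primary heart rate conclusion does not depend on it.

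**What to change.** Rewrite the last sentence of the HRV section. The model should be within-participant, with condition (taVNS, sham) by time (pre, during, post). Name the condition-by-time interaction, reported as the taVNS-minus-sham difference in change from pre, as the test of the taVNS effect on each HRV index. If the present phrase is a truncation, complete it and still name the tested term.

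The cost is a change of wording. The same ECG recordings are already planned in both sessions, so no participants, visits or measurements are added.
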